### Sample Size Calculation

We used STATA Version 16 (StataCorp) to calculate the ideal sample size. We attempted to enroll 108 participants in total, allocating 54 to each treatment arm. We estimate that a sample size of 86 participants would be sufficient to detect a mean difference between arms of 55.1 meters in the 6MWT according to the study by Liu et al [11] considering a 95% CI and 90% power. Assuming a potential 20% rate of rejection or loss to follow-up, we aimed to achieve a sample of 108 participants.

### Ethics Approval

Ethical approval of the study protocol and informed consent form was obtained from the Institutional Review Board at Universidad Peruana Cayetano Heredia (#202852) and HNCH (#085-2020). Likewise, any changes in the protocol were reported to the mentioned ethics committees. Written informed consent was requested from all participants prior to any data collection. To protect participants’ confidentiality, all collected data of clinical assessments were linked to a unique ID code. Data were registered in paper form and electronically. The electronic information was stored, backed-up, and secured by password protection in the RedCap server. Paper forms were archived in secure locked cabinets in the HNCH. All confidential information, including participants’ contact details or other sensitive data, was only accessible to authorized staff from the project. Long-term data management complied with Universidad Peruana Cayetano Heredia research policy. The Peruvian National Health Institute reviewed the protocol and determined that it was exempt from review by the Ethics Committee due to the nonpharmacological nature of the intervention.

### Benefits and Risk of Participation

Both control- and intervention-arm participants benefited from the study. These benefits included education and counseling on respiratory disease risk factors, reporting of pulmonary function test results by a specialist physician, and referral to trained personnel if necessary.

Potential risks of respiratory rehabilitation were oxygen desaturation, palpitations, sweating, arrhythmias, chest tightness, shortness of breath, and muscle aches. Potential risks of psychological support were symptom substitution, dependence on the physiotherapist, stigmatization, problems in social relationships or even separation, as well as alcohol or drug abuse, deliberate self-harm, and suicidal ideation or attempts. Adverse events of the interventions were collected after participants provided informed consent and were duly enrolled in the study. If adverse events were detected, the field staff immediately notified the study coordinator and the management protocol was activated.

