## Methods

### Study Design

WAYRA (the word for air in the Quechua language) was a randomized, controlled, open-label, two-arm clinical trial that evaluated the efficacy of a 6-week home-based respiratory physiotherapy and telephone-based psychological program compared to usual posthospital care provided by a public Peruvian hospital, aimed at improving exercise tolerance, lung function, mental health, and quality of life (QoL) outcomes. A baseline assessment was conducted at hospital discharge, with two follow-ups at week 7 and 12 (Figure 1). Due to the nature of the rehabilitation interventions, blinding of participants and the researchers was not possible; however, the data scientist conducting the data analysis was blinded. The trial was registered at ClinicalTrials.gov (NCT04649736).

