### Comparison Groups

#### Intervention Arm

The intervention consisted of 12 sessions of home-based respiratory rehabilitation and 6 sessions of weekly psychological support delivered through telephone home calls throughout a period of 6 weeks. Participants began the rehabilitation program no later than 1 week after hospital discharge.

Respiratory rehabilitation consisted of 12 sessions (1-3 per week depending on the participant’s availability) performed at home under trained physiotherapist guidance. Each respiratory rehabilitation session lasted approximately 1 hour. In the first rehabilitation session, the physiotherapist brought the necessary equipment to perform the exercises (1-kilogram abdominal weight and a small rubber ball). In each session, the participant performed the following exercises: respiratory muscle training by breathing through pursed lips and breathing education exercises, coughing exercises to produce effective coughs, diaphragm training by teaching diaphragmatic contractions in the supine position with a light weight placed on the anterior abdominal wall, and stretching exercises whereby the participant was placed in a supine or lateral position with the knees bent to correct for lumbar lordosis. In addition, participants performed arm movements in flexion, horizontal extension, abduction, and external rotation. Participants were instructed to perform pursed-lip breathing and effective coughing on the days they did not receive assisted therapy, with a frequency of 30 times per day. The day of nonattendance at respiratory therapy was recorded. Given the risk of exposure to COVID-19, physiotherapists followed a strict biosafety protocol involving the use of personal protective equipment and a thorough disinfection process at each visit. In addition, rehabilitation was ideally performed in a well-ventilated room and the participant wore a surgical mask during visits as an extra protective measure.

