The psychological support intervention consisted of an introductory session (Session 0) and 6 1-hour structured sessions based on emotion-centered problem-solving therapy (EC-PST). A trained licensed psychologist provided these sessions once a week by telephone home calls following the guidelines of the Inter-Agency Standing Committee (IASC) on Mental Health and Psychosocial Support in Humanitarian and Disaster Emergencies of the World Health Organization [18]. The EC-PST is an update of the classic problem-solving therapy that emphasizes guiding patients to better understand and manage their emotional reactions to stressful events as a means of coping with the negative effects of these stressors [19]. EC-PST reviews four components: (1) Planful Problem Solving, (2) Overcoming Brain Overload, (3) Enhancing Motivation for Action, and (4) Stop and Slow Down. In addition, we provided each participant with a printed workbook that included the themes and topics that were developed in each session, and the psychologist recorded the main points of the session using an adhoc evaluation form. Table 2 summarizes the objectives of each session.

**Table 2 table2:** Psychological support objectives.

Session	Content	Objectives
0	Introductory session and psychological history	Take the participant’s psychological medical history; evaluate stressful events, consequences, and the participant’s perception of what they are experiencing, through the functional behavioral analysis
1	Psychoeducation session	Provide information on the types of problem orientation and problem-solving styles; identify the problem-solving style employed by the patient
2	Toolbox training 1 “Stop and Slow Down”	Teach the “Stop and Slow Down” tool to better modulate emotional reactions to stressful stimuli. Strategies included are counting, guided imagery or visualization, deep breathing, “fake” yawning, conscious meditation, relaxation exercises, deep-muscle exercise or conscious walking, talking to someone, prayer, and the DAPA^a^ Method for Emotional Regulation

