#### Control Arm

Participants assigned to the control arm received posthospital usual care delivered by a Peruvian public hospital consisting of discharge recommendations and a telephone follow-up for 14 days provided by the same hospital. Although there are no national guidelines for standardized discharge indications in Peru, many hospitals recommended patients to perform home breathing exercises and symptomatic respiratory treatment. There are currently no diagnostic or follow-up plans for patients that experience or develop mental illness or a strategy for respiratory or psychological rehabilitation in most hospitals in Peru. We collected data about any additional nonstudy therapies that participants may have received from any internal or external health care provider.

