#### Secondary Outcomes

A trained physician measured forced expiratory volume in the first second (FEV1), forced vital capacity (FVC), and the FEV1/FVC ratio using a portable spirometer (Easy-On-PC). These spirometers are frequently used in pulmonary research because their calibration remains stable over time [23]. We aimed to obtain at least three acceptable and two reproducible tests following joint recommendations of the American Thoracic Society and European Respiratory Societies [24] or until the participant was no longer able to tolerate the procedure. Results were recorded on a secure interface (EasyOnConnect) on a personal computer.

For mental health and QoL assessments, participants responded to questionnaires administered by a trained health worker. We used PHQ-9, GAD-7, and IES-R questionnaires to assess mental health, including depression [25], anxiety [26], and posttraumatic stress disorder symptoms [27], respectively. Mental health questionnaires were administered at 2, 4, 7, 8, and 12 weeks after hospitalization by telephone home calls. We used the SF-36 v2 [28] and EQ-5D [29] questionnaires to measure QoL at 7 and 12 weeks after discharge. The psychometric properties of the SF-36 questionnaire have been widely studied and consist of 36 items assessing 8 dimensions: physical functioning, physical role, bodily pain, general health, vitality, social functioning, emotional role, and mental health [30]. The details of the measurements for the primary and secondary outcomes are summarized in Table 3. We used the SGRQ to assess respiratory symptoms, an instrument recommended to measure changes in respiratory health following interventions [31]. We measured respiratory symptoms at 7 and 12 weeks after hospital discharge (Table 1).

**Table 3 table3:** Outcomes and instruments in the WAYRA study.

Outcome	Instruments
Pulmonary function	6-minute walk test, spirometry [20]
Respiratory symptoms	St. George’s Respiratory Questionnaire (SGRQ) [31]
Depressive symptoms	Patient Health Questionnaire (PHQ-9) [25]
Anxiety symptoms	Generalized Anxiety Disorder (GAD-7) [26]
Posttraumatic stress disorder	Impact Event Scale-Revised (IES-R) [27]
Quality of life	36-Item Short-Form Health Survey [28], EuroQol-5D (EQ-5D) [29]

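### Adverse event counts collected as described cannot be compared between arms: collection is tied to the interventions and to detection by unblinded field staff, and one arm has 19 extra staff contacts

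*Protocol article*

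**What the plan says.** The Protocol article deals with harms under Benefits and Risk of Participation. It lists potential risks of respiratory rehabilitation (among them desaturation, palpitations, arrhythmias and shortness of breath) and of psychological support (among them self-harm and suicidal ideation or attempts). It lists none for usual care. It then says: "Adverse events of the interventions were collected after participants provided informed consent and were duly enrolled in the study". Reporting depends on detection: "If adverse events were detected, the field staff immediately notified the study coordinator and the management protocol was activated". The Study Design section says that participants and researchers were not blinded and that the data analyst was.

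Contact with staff differs by arm:

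- Intervention Arm, physiotherapy: "Respiratory rehabilitation consisted of 12 sessions (1-3 per week depending on the participant’s availability) performed at home under trained physiotherapist guidance".
- Intervention Arm, psychology: "The psychological support intervention consisted of an introductory session (Session 0) and 6 1-hour structured sessions", delivered by telephone.
- Control Arm: usual care "consisting of discharge recommendations and a telephone follow-up for 14 days provided by the same hospital".
- No arm restriction stated: "Mental health questionnaires were administered at 2, 4, 7, 8, and 12 weeks after hospitalization by telephone home calls". Study Design and Table 1 add follow-up assessments at weeks 7 and 12.

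**The concern.** A fair comparison of adverse events needs the same definition and the same opportunity to record them in each arm. The stated rule secures neither.

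First, an event that belongs to the interventions has no clear meaning for someone receiving usual care. Several listed risks, shortness of breath above all, are also ordinary consequences of severe COVID-19. Whether an individual event came from the programme or from the illness cannot be settled by judgement in one arm. An excess over a control arm that was asked the same questions could show it.

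Second, events enter the record when staff detect them, and staff meet intervention participants far more often. A raw table by arm would tend to show more events under the programme even if it caused none.

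The Statistical Analyses section says the trial will inform whether to proceed to phase III, and the Discussion hopes it will be a basis for further trials. Readers are therefore likely to look at adverse events by arm even though no formal test of them is planned.

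**Working it through.** **1. Extra contacts in the intervention arm.** The article gives the parts, not the sum.

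- Home physiotherapy sessions: 12.
- Psychology calls: Session 0 plus 6 = 7.
- Total: 12 + 7 = 19. If Session 0 is not counted as a separate contact, 12 + 6 = 18, which changes nothing below.

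**2. Contacts common to both arms after allocation.** There are mental health calls at weeks 2, 4, 7, 8 and 12 (5) and assessments at weeks 7 and 12 (2). The common count is 5 if the week 7 and 12 calls coincide with the assessments, and 5 + 2 = 7 if they are separate.

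- Coinciding: 5 + 19 = 24 against 5, ratio 24 / 5 = 4.8.
- Separate: 7 + 19 = 26 against 7, ratio 26 / 7 = 3.7.

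The hospital's 14-day telephone follow-up is left out. It is run by the hospital, is not described as study data collection, and no number of calls is given.

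**3. What unequal contact can do by itself.** Let each of k contacts have the same chance d of recording an event, independently and equally in both arms, so that there is no true difference. The share of participants with at least one recorded event is 1 − (1 − d)^k. The documents give no value for d; the values below are assumptions.

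| Assumed d | 24 vs 5 contacts | 26 vs 7 contacts |
|---|---|---|
| 2% | 38% vs 10% | 41% vs 13% |
| 5% | 71% vs 23% | 74% vs 30% |
| 10% | 92% vs 41% | 94% vs 52% |

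For example, at d = 5%: 1 − 0.95^24 = 0.71 and 1 − 0.95^5 = 0.23. The size depends on d. The direction follows from the documented schedule.

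**4. Background symptoms.** The Introduction gives dyspnea after acute illness in 24% to 36% of patients with COVID-19. With 54 per arm (Sample Size Calculation), 54 × 0.24 = 13.0 and 54 × 0.36 = 19.4, so about 13 to 19 participants per arm could report breathlessness with no programme effect. This figure is for patients with COVID-19 in general; the same section says complications are more frequent after hospitalization.

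**5. What is measured alike in both arms.** With no arm restriction stated, PHQ-9, GAD-7 and IES-R are taken at weeks 2, 4, 7, 8 and 12, and SGRQ, spirometry and the 6-minute walk at weeks 7 and 12. These show average worsening in mood, anxiety, trauma symptoms, respiratory symptoms, lung function and exercise capacity. They do not count discrete events such as arrhythmia, readmission or death.

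**The case against.** Three stronger readings are tempting, and the article supports none of them.

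- A reader might infer that events are recorded in the intervention arm only, so that the control count is close to zero. The sentence names no arm, does not contain the word only, and refers to participants after enrolment.
- A reader might infer that field staff must judge an event attributable before it is recorded. The trigger described is detection; no causality step is set out. Tying events to the interventions invites such a judgement but does not state one.
- A reader might infer that the trial can say nothing about the programme's safety. Intervention-arm events can still be described, and the common-schedule measures give between-arm evidence on deterioration in several of the listed risk areas.

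It can also be said that safety is not a stated objective, that no between-arm adverse event test is planned, and that the phase III decision is tied to a one-sided 80% CI rather than to event counts. Unequal contact is inherent in testing an added programme against usual care. This is also a condensed article, so forms and question schedules may sit in the full protocol, and their absence here is no fault.

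All of that stands, and it limits the point to comparability. It does not remove it: the one collection rule that the article does state is defined by treatment and by detection, and followed as written it gives non-comparable counts. If the full protocol asks both arms the same questions, the published sentence misdescribes it and should be corrected.

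**Conclusion.** The point holds as a limit on what the adverse event data can support. Collected as worded, counts are not comparable between arms: intervention participants have 24 contacts against 5, or 26 against 7, and the definition refers to treatments that controls do not receive. Background dyspnea of 24% to 36% means that attribution cannot separate programme harm from illness.

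The contact counts are planned numbers taken from the article and are firm. The percentages of participants with a recorded event rest on an assumed, equal and independent chance per contact; they show direction and possible scale and do not forecast this trial's results. The conclusion also assumes that no common adverse event enquiry exists in documents not shown. The primary and secondary efficacy comparisons are unaffected.

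**What to change.** As a collection rule: record all adverse events in both arms regardless of attribution, including readmission and death, using one fixed set of questions at the calls already scheduled at weeks 2, 4, 7, 8 and 12. Base any between-arm comparison only on events elicited at those calls. List events detected at physiotherapy or psychology sessions separately, for the intervention arm.

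The article reports that recruitment and data collection ran from October 2020 to June 2021, so new questions may come too late for this trial. The reporting part can still be applied: state whether and how control participants were asked about adverse events. If a common enquiry was made, confine the comparison to it. If none was made, describe intervention-arm events only and report no between-arm adverse event comparison. The full collection rule would then apply to any follow-on trial.

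The cost is slightly longer calls and more unrelated events to log, with no new visits. For this trial it is a clarifying sentence and a reporting restriction.

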## Results

The trial, which obtained funding in July 2020, was approved by the Institutional Review Board on September 2, 2020. Data collection began in October 2020. Enrollment of participants began in October 2020 and was completed in June 2021. Results of the study are expected to be published by the end of 2022.

## Discussion

### Summary

WAYRA is the first randomized controlled trial evaluating integrated pulmonary and mental health rehabilitation for hospitalized COVID-19 survivors in a low- and middle-income country setting. Through this trial, we gained experience in implementing a remote rehabilitation program in a resource-limited country and will generate evidence on pulmonary, mental health, and QoL alterations following COVID-19 the first 3 months after hospitalization. We hypothesize that participation in the combined program will improve pulmonary, physical, and mental health outcomes. We hope that our study will provide a reliable basis for further clinical trials focused on comprehensive rehabilitation in patients hospitalized for severe COVID-19 and other lung diseases.

The burden of long-term complications of COVID-19 will increase because, although several countries have achieved broad vaccination coverage, newly emerging variants may be resistant to vaccines [33]. The most frequently affected systems are respiratory and physical, although psychological symptoms are also common [3]. Despite this, there are still few published studies that have proposed strategies for COVID-19 survivors with long-term complications and far fewer that include mental health support. There are approximately 200 trials registered with ClinicalTrials.gov evaluating rehabilitation programs for COVID-19 survivors; most include pulmonary rehabilitation, whereas only a few have a psychological component [34].

### Strengths and Limitations

The main strength of this study is that the calculated sample size has the power to detect a clinically significant difference between the groups. Nevertheless, this study has some limitations to be considered. First, mental health and QoL outcomes will be assessed with screening tools. Second, this trial has an open-label design due the nature of the intervention.

### Conclusions

In conclusion, the COVID-19 pandemic will result in millions of people prone to develop respiratory and mental health sequelae worldwide, and health systems are not prepared to respond adequately to this situation. Little evidence exists on rehabilitation strategies, and most of the existing evidence does not come from low- and middle-income countries that face additional challenges compared with developed countries. The clinical trial described in this protocol will generate useful evidence to develop effective interventions to benefit patients after COVID-19, and will serve as a basis to help plan future studies evaluating pulmonary rehabilitation strategies and mental psychological support.

## Appendix

Multimedia Appendix 1 Informed consent form.

Multimedia Appendix 2 CONSORT-eHEALTH v1.6.1

## Abbreviations

6MWT: 6-minute walk test
6MWD: 6-minute walk distance
EC-PST: emotion-centered problem-solving therapy
EQ-5D: EuroQol-5D
FEV1: forced expiratory volume in the first second.
FVC: forced vital capacity.
GAD-7: Generalized Anxiety Disorder
HNCH: Hospital Nacional Cayetano Heredia
IASC: Inter-Agency Standing Committee
IES-R: Impact Event Scale-Revised
MoCA-BLIND: Montreal Cognitive Assessment, visual impairment version
PHQ-9: Patient Health Questionnaire
QoL: quality of life
SF-36: 36-Item Short Form health survey
SGRQ: St. George’s Respiratory Questionnaire
